Project staff will be placed at hospitals and health centers to which children in the trial are likely to be taken if they develop a febrile illness. A finger-prick blood sample will be taken from any child in the trial who presents at one of these designated centers with a temperature of 37.5 0C or higher or a history of fever in the previous 24 hours for a rapid malaria antigen test, preparation of a blood film and collection of a filter paper sample for molecular studies. Children who are febrile and who have a positive antigen test will be treated with the nationally recommended first line treatment for malaria. Records will be kept of any study child who is admitted with severe malaria. In addition, 150 children will be visited at home each week and a blood film obtained regardless of whether or not the child is febrile to determine the impact of IPT on the prevalence of parasitemia throughout the malaria transmission season. A baseline cross-sectional survey will be conducted before treatment allocation in a random sample of children for the estimation of the prevalence of genetic markers of resistance to SP and AQ. These children will not take part in the trial. A cross-sectional survey will be undertaken at the end of the transmission season to determine the parasite prevalence rate, hemoglobin concentration of all children in the study and the prevalence of markers of resistance in children with positive parasitemia.

During the following dry season, when little malaria transmission is likely to occur, passive surveillance will be maintained at hospitals and health centers but active surveillance will be reduced to 300 visits each month. The following malaria transmission season, intensified surveillance will be re-established to determine if the combined use of ITNs and IPT had any impact on the development of naturally acquired immunity to malaria, reflected in an increased number of cases of malaria (rebound malaria) in children in the ITN + IPT group.

Clinical and laboratory methods will be standardized across sites as far as possible. An overall analysis plan will be prepared before the randomization code is broken. The trial is designed to have 90% power to detect a 20% reduction in the incidence of clinical attacks of malaria at each site in children who receive IPT in addition to an ITN. Using pooled data from each site, the trial will have 90% power to detect a 50% reduction in hospital admissions with severe malaria.

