*Boussé district, Burkina Faso.* Boussé is a rural area situated 40 kilometers northwest of the capital Ouagadougou. The entomological inoculation rate (EIR) is less (around 200 infectious bites per year). Most transmission occurs between July and October. At least 90% of children aged 6 – 59 months carry malaria parasites during this period. It is estimated that each child under five years of age experiences about 0.8 clinical attacks of malaria per year. ITN coverage is currently low.

*In Mali, the trial will take place in the following health centres: Djoliba, Siby and Ouelessebougou in Kati administrative region. Djoliba is located in a rural setting 60km southwest of Bamako with a population of 30000 inhabitants. Siby is located 45 km west of Bamako and the health centre covers a population of 15,232 inhabitants. Ouelessebougou is situated 80 km south of Bamako and provides service to 34,600 inhabitants*. The rainy season extends from June to October with an annual rainfall of 800 – 1200 mm. Malaria transmission is seasonal. The EIR is in the range of 100-150 infectious bites per person per season. Children have about 2 clinical attacks of malaria per year and the prevalence of parasitaemia at the end of the transmission season is about 70%. ITN usage is low.

Characteristics of the two study sites are summarized in Table 1.

**Table 1**. Characteristics of the study sites.

Variable Site

Bousse Doliba, Siby and Ouelessebougou **

Demographic 74,000 -

surveillance

Transmission June- Nov July-Nov

season

Rainfall [contact]

mm/year

Net coverage in

children < 5 years

Untreated < 3% <3%

Treated < 1% <7%

Clinical attacks per 0.8 2

year in children < 5 years

Parasite prevalence 85-95% 40 - 75%

in children < 5 years

First-line treatment AL AS/AQ or AL

of malaria***

** Because of an impending malaria vaccine trial it may be necessary to move the IPTc

study to an adjacent community.

*** AQ = amodiaquine; AS = artesunate; AL = artmether/lumefantrine (Co-Artem)

*Recruitment and randomization*

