The incidence of clinical malaria in unprotected children aged 3 – 59 months living in the study area detected by passive surveillance is likely to be in the range of 1.0 -2.0 clinical attacks per year and the incidence in those sleeping under an ITN will be about one half of this (0.5 to 1.0 clinical attacks per year). Assuming that children experience an average of 0.5 attacks per year of sufficient severity to present to a health facility, and the need to detect a 20% reduction in this incidence (ie. from 0.5 to 0.4 attacks per year) in children who receive IPT, the smallest reduction that would be likely to make IPT a worthwhile investment, and allowing for a 20% loss to follow-up, approximately 2,000 children (1,000 in each arm) will be required at each site to give a study with 90% power and 95% precision. A study of this size will have greater than 90% power to detect a 20% reduction in the estimated prevalence of parasitemia from 50% to 40% at the end of the rainy season. The study will have a slightly lower power to detect a 20% increase in the incidence of malaria or the prevalence of parasitemia during the second period of observation due to some loss to follow-up (likely to be in the range of 10 – 20 %). Pooling of data across sites will increase the power of the study to detect a small rebound effect.

It is estimated that the rate of hospital admissions with malaria will be in the range of 20 to 60 per 1,000. Assuming a median incidence rate of 40 per 1,000, approximately 120 admissions with severe malaria might be anticipated in children in the control arm of the study. The study will, therefore, have at least 90% power to detect a 50% reduction in admission with severe malaria (from 40 to 20 per 1,000). Initially, estimation of the impact of IPTc on admission with severe malaria was to be assessed using pooled data from three sites (MRTC, CNRFP and Navrongo Health Research Centre) and that the trial in Navrongo was suspended in June 2008 (due problems in getting ethical clearance), the number of children (2,000) who were to be enrolled at the Navrongo site has now been split between CNRFP and MRTC. Therefore the number of children to be enrolled in each of the two sites has been increased to 3,000 (1500 per arm). The study will not be powered to detect an effect on mortality but deaths will be recorded and investigated for safety reasons.

*Insecticide treated nets*

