4.1 The number of children to be enrolled in the trial in Navrongo has been split between MRTC Mali and CNRFP, Burkina Faso as the trial will now be conducted in these two sites only. The number of children to enrolled at each of these two sites is now increased to 3,000 children (1,500 per arm). The initial sample size of 2000 children per site was estimated to have adequate power to measure the protective efficacy of IPTc on malaria morbidity at each site and to pool the data from all three sites (6,000 children) to measure the impact of IPTc on admission to hospital with severe malaria. Therefore, in order to have adequate power to measure the effect of IPTc on hospital admissions with malaria, we have to increase the sample size from 2,000 to 3,000 in Burkina Faso and Mali.

4.2 The number of children to be enrolled in the weekly and the monthly surveys for the effect of IPTc on the prevalence of malaria infection and the number of samples to be analysed per site to assess the impact of IPTc on the prevalence of markers of resistance to SP and AQ have been re-adjusted by redistributing samples that were to be collected at the Navrongo site between CNRFP and MRTC. Thus site will collect 2500 more samples over the study period (see table 3 below).

1. Baseline survey of markers of resistance to SP and AQ

A random sample of children from the study villages’ census lists will be selected for the baseline survey of the prevalence of markers of resistance to SP and AQ (about 400-500 children per site). Children who will be involved in this survey will not take part in the trial of intermittent preventive treatment, but will be given and ITN. Initially, these children were to be recruited from neighbouring villages.

1. Safety of SP and AQ (Monitoring of adverse events)

The initial plan was to conduct weekly visits in a random sample of 100 children to monitor adverse events. It has now been amended that adverse events will be assessed on days 0, 1 and 2 of IPTc administration and the day after the last dose of IPTc administration in all children enrolled in the study. Adverse events that may occur after day 3 post IPTc will be recorded on day 0 of the next round of IPTc administration. This option provides the opportunity for monitoring adverse events in all study children.

1. Intermittent Preventive Treatment administration

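### The 2,000-per-site requirement for the primary endpoint does not include the 20% loss it claims to allow for; the 3,000 enrolled does reach 90% power, but with almost no reserve at Boussé

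*Combined protocol and SAP*

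**What the plan says.** The Executive Summary sets the target: "The trial is designed to have 90% power to detect a 20% reduction in the incidence of clinical attacks of malaria at each site". The Sample size section (part IV) gives the inputs. Incidence in unprotected children is "likely to be in the range of 1.0 -2.0 clinical attacks per year", and nets are expected to halve it. The control rate used for sizing is at the low end of the halved range: "Assuming that children experience an average of 0.5 attacks per year of sufficient severity to present to a health facility". The effect is a 20% reduction ("ie. from 0.5 to 0.4 attacks per year"), and the calculation is described as "allowing for a 20% loss to follow-up". The result is that "approximately 2,000 children (1,000 in each arm) will be required at each site to give a study with 90% power and 95% precision".

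The next paragraph of the section raises enrolment to 3,000 per site (1,500 per arm), because the 2,000 children of the suspended third site were divided between the two that remain. The reason given is the pooled severe-malaria comparison. Item 4.1 of the amendment summary gives the same reason and says of morbidity: "The initial sample size of 2000 children per site was estimated to have adequate power to measure the protective efficacy of IPTc on malaria morbidity". The 2,000 sentence stays in the current Sample size text.

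Under Study sites and populations, the Boussé entry reads: "It is estimated that each child under five years of age experiences about 0.8 clinical attacks of malaria per year". Table 1 repeats the 0.8 and puts treated-net coverage there below 1%. Mali is given 2 attacks per year.

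**The concern.** Two things do not fit. First, 1,000 per arm lies close to what the comparison needs before any loss, although the sentence says that loss has been allowed for. Second, the rate given for one of the two sites falls below the range that the calculation assumes for unprotected children.

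The plan promises an answer on the primary endpoint at each site separately, so the per-site requirement matters. As the text stands, a reader would take it that each site has 1,000 children more than the primary endpoint needs. If recruitment fell short, or loss exceeded 20%, anyone judging whether the site could still answer its main question would be using the wrong threshold.

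**Working it through.** **Inputs.** Control rate 0.5, IPT rate 0.4, loss 20%, power 90%, 1:1 allocation, all from Sample size. I read the section's 95% precision as a 5% significance level. Two-sided testing, one year of observation per child and Poisson counts are my assumptions.

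**Formulas.** Child-years per arm = (1.96 + 1.2816)² × (r0 + r1) / (r0 − r1)². Power = Φ(|r0 − r1| / √((r0 + r1)/n) − 1.96), where n is child-years per arm.

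**The plan's own figure.**
- Before loss: 10.507 × 0.9 / 0.01 = 946 child-years per arm.
- After 20% full loss: 946 / 0.8 = about 1,182 per arm, about 2,364 per site.
- The stated 1,000 per arm is not reproduced once loss is included.

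**Power at 1,000 per arm, 0.5 v 0.4.**

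| Treatment of loss | Child-years per arm | Power |
| --- | --- | --- |
| No loss | 1,000 | 91.5% |
| 20% loss spread evenly over the year | 900 | 88.5% |
| 20% lost, contributing no time | 800 | 84.6% |

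With evenly spread loss the requirement is 946 / 0.9 = about 1,051 per arm, about 2,102 per site. A one-sided 5% test with full loss gives 90.9%.

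**Boussé.** Halving 0.8 gives 0.4, and a 20% reduction gives 0.32. Before loss: 10.507 × 0.72 / 0.0064 = 1,182 child-years per arm. After 20% loss: 1,182 / 0.8 = about 1,478 per arm, about 2,956 per site. The margin within 3,000 is 3,000 − 2,956 = 44 children. Put as loss, 1 − 1,182/1,500 = about 21%, so power drops below 90% once loss passes about 21%.

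**Enrolled size, year 1.** 1,500 per arm less 20% leaves 1,200 child-years.
- 0.5 v 0.4: 0.1 / √(0.9/1,200) = 3.651, power 95.5%.
- 0.4 v 0.32: 0.08 / √(0.72/1,200) = 3.266, power 90.4%.

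**Year 2, a 20% increase at Boussé (0.40 v 0.48), 1,500 per arm.**
- Total loss 10% (1,350 left): 88%.
- Total loss 20% (1,200 left): 84%.
- Both sites pooled, each conservatively taken at 0.4 per year with 20% loss (2,400 per arm): 0.08 / √(0.88/2,400) = 4.178, power 98.7%.

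**Repeat attacks.** If children differ in underlying risk, the variance term becomes r0 + r1 + (r0² + r1²)/k. The documents give no k. Taking k = 2 and k = 1 as an assumed range, year-1 power at Boussé with 1,200 child-years per arm is 85% and 80%.

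**The case against.** The strongest reply is that 2,000 is not the size of the trial. The Executive Summary, the Recruitment section and Sample size itself all enrol 3,000 per site, and on the formula above that meets the 90% target at both 0.5 and 0.4 per year. This stands. A reader might infer from the 85% that the trial is underpowered for its primary endpoint in year 1; the documents do not support that.

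A reader might also combine 1,000 per arm with the halved Boussé rate and get 76%. That pairs a size which is not being enrolled with a rate the documents never state. The 0.4 is derived, and the Boussé entry does not say whether 0.8 counts only attacks that reach a health facility, which is what the 0.5 describes. The uncertainty is real, but if 0.8 counts all attacks, the passively detected rate would be lower than 0.4, not higher.

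The 85% rests on choices the plan leaves open. Evenly spread loss narrows the gap to 88.5%, and a one-sided test would close it. But no one-sided test is stated, and year 2 looks for an increase in the same endpoint, so both directions matter.

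On year 2, the section already says that power will be slightly lower and that pooling will help, and the 84 to 88% agrees with that. Figures of 75 to 80% follow only if the year-2 loss is added to a full 20% in year 1, which the documents do not say. The range for k is likewise from outside the documents, and the detailed analysis plans are deferred to approval by the Data Safety and Monitoring Board before the code is broken, so the lack of a model here is not in itself a fault.

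**Conclusion.** The 2,000-per-site sentence is wrong as written: the requirement on its own inputs is about 2,364 with a two-sided test and full loss, and 2,000 gives about 85% (88.5% with evenly spread loss). The assumed range of 1.0 to 2.0 also conflicts with Boussé's 0.8.

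Neither fault shows a lack of power at the enrolled size in year 1. What changes is the role of the increase to 3,000. If 0.8 counts facility-presenting attacks and nets halve it, about 2,956 of the 3,000 children at Boussé are needed for the primary endpoint itself, and the reserve there is about 44 children or one percentage point of loss. That reserve exists only under Poisson counts; any between-child variation uses it up. The arithmetic for the 2,000 sentence is firm given a two-sided test. The Boussé figures depend on the derived 0.4.

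**What to change.** In the Sample size section:

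1. Replace the 2,000 figure with 946 child-years per arm before loss and about 1,182 per arm (about 2,364 per site) after 20% loss, and state that the test is two-sided at 5%.
2. Reconcile 0.8 at Boussé with the 1.0 to 2.0 range, and say whether 0.8 counts attacks that present to a facility. If 0.4 is the working rate there, state that about 1,478 per arm is needed for the primary endpoint, so that the 3,000 is not attributed to severe malaria alone.
3. State power by site at 1,500 per arm. For year 1: 95.5% at 0.5 per year and 90.4% at 0.4. For year 2 at Boussé: about 84 to 88% for 0.40 v 0.48 with 10 to 20% total loss, with the pooled figure alongside.
4. Say that these figures assume Poisson counts, and show a range for between-child variation.

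In the analysis plans, specify a negative binomial model or child-level robust standard errors for attack counts.

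The cost is wording and one analysis specification. No extra children and no change in field procedures are needed. The downside is that the stated requirement rises and the small reserve at Boussé becomes visible.

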After village meetings have been held in each study area to explain the nature of the trial, a census of children under five years of age resident in the study area will be conducted. At each site, approximately 3,100children aged 3 – 59 months will be selected randomly from the census list for initial screening. The families of these children will be visited by a member of the field team and invited to participate in the study. If a family agrees that a child can join the trial, signed, informed consent will be obtained from a parent or guardian in the presence of an independent witness. Children will then be screened for their eligibility to join the trial until 3,000 have been entered. Screening will include administration of a questionnaire which asks about previous illnesses, clinical examination and measurement of height and weight.

Inclusion criteria will be –

- Age 3 – 59 months.
- Permanent residence in the study area with no intention of leaving during the surveillance period.
- Provision of informed consent.

Exclusion criteria will be -

- Temporary residence in the study area.
- Absence of informed consent.
- Presence of a severe, chronic illness such as severe malnutrition or AIDS, likely to interfere with evaluation of the trial results.
- A history of a previous, significant adverse reaction to either of the study drugs.

An acute illness, such as malaria, will not be an exclusion criterion. Such illnesses will be treated appropriately, the child randomized and retained in the trial. Children who are invited to join the trial but who are excluded for one of the reasons indicated above will be given an ITN but will not be followed further.

Children will be individually randomized using a standard computer program which gives randomization within blocks of varying number. Separate randomization lists will be generated for each site. In order to reduce the chances of the investigators becoming aware of the drug code during the course of the trial, for example because of an increased incidence of vomiting in one group, ten randomization groups will be used, five for active drugs and five for placebo. Children enrolled in the trial will be issued with a photo identity card and the parents or guardian will be asked to present this whenever their child is taken to a health centre or hospital to ensure that the child is seen by a member of the study team.

*Sample size*

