Immediately after recruitment to the trial, the mother or guardian of each study child will be provided with a long lasting, insecticide treated net (LLIN) that is marked with an identification number. Instructions will be given to the parent or guardian on how to use the net and the importance of using the net on the bed/sleeping place of the study child will be emphasized. If a child already has a net, this will be replaced and the old net returned to the family for their use. Utilisation of LLINs by study children will be monitored during home visits made to collect blood films (see below) and during the cross-sectional survey conducted at the end of the malaria transmission season.

*Intermittent preventive treatment*

Study children will be treated with a course of SP + AQ or matching placebos on three occasions during the malaria transmission season. Drugs will be pre-packaged to facilitate administration. Monthly doses will be timed to cover the peak transmission season at each site, July/August/September in Burkina Faso and Aug/Sept/Oct in Mali. Doses of AQ and SP will be based on weight as shown in Table 2. AQ will administered on the base of 10 mg/kg daily for 3 days and SP will administered as a single dose of 25mg/kg of sulphadoxine + 1.25 mg of pyrimethamine. Full tablets containing the exact daily dose (AQ) or the dose for a full course (SP) will be manufactured to avoid having to split tablets which may lead to administration of inadequate doses.

**Table 2**. Dosage of study drugs.

Weight groups Amodiaquine* SP**

Tablets (Daily dose) tablets (single dose) **

Sulfadoxine Pyrimethamine

5-9 kg 70 mg 175 mg 8.75 mg

10-18 kg 140 mg 350 mg 17.5 mg

19 kg+ 220 mg 550 mg 26.25 mg

Note. * Tablet given for 3 days;  ** tablet given for 1 day

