**Protocol amendments**

**Date 20th June 2008**

**Amendments to version 1 of the protocol (20th June 2008)**

**Summary of changes made**

The trial steering committee comprising staff from the London school of Hygiene and Tropical medicine and the trial Principal investigators at the sites in Africa met in March and June 2008 and made the following amendments to the protocol the version of the protocol as described below. These amendments will be submitted to Ethics committee of institutions participating in the trial.

1. Dosage of sulfadoxine-pyrimethamine and amodiaquine

It was indicated in the protocol that sulphadoxine-pyrimethamine (SP) and amodiaquine (AQ) dosage will be based on child’s age. Four age categories were constituted. However, considering the difficulty of correctly estimating child’s age in rural communities, the study steering committee agreed that drug administration based on child’s weight will be more appropriate in routine programme settings. Therefore three weight groups have been constituted (5-9 kg; 10-18 kg and 19 kg and over). The exact daily dose (AQ: 70mg for 5-9kg, 140 mg for 10=18kg and 220 mg for 19+kg; SP: 175 mg + 8.75 mg for 5-9 kg; 350 mg +17.5 mg for 10-18 kg and 550 mg + 26.75 mg for 19+kg) will be manufacturing for each weight to avoid breaking tablets in halves or quarters, which may results in inadequate dosage of drugs.

1. Trial sites

Ethical clearance was obtained for the conduct of the study in Burkina Faso and Mali. The third trial site (Navrongo Health Research Centre) was not successful in getting ethical clearance from the Ghana Food and Drug Board (FDB). The FDB raised some queries which the site is currently addressing. However, it is feared that obtaining ethical clearance after re-submission of a revised protocol to the FDB is likely to take at least 2 months which will cause a significant delay in the implementation of the study. Therefore it was agreed to suspend the trial in Navrongo. Consequently, sections relating to the Navrongo Health Research Centre have been removed from the protocol.

1. Randomization

The first version of the protocol indicates that randomisation will be done in 8 blocks (4 blocks per group). To minimise risk of “unblinding” of research staff, the number of blocks was increased to 5. Thus, randomization will now be done in permuted blocks of 10 (5 blocks per group).

1. Samples size

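### The two SP components in the 19 kg+ row of Table 2 do not fit the protocol's own per-kilogram basis at any one weight, and children eligible by age but under 5 kg have no dose row

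*Combined protocol and SAP*

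**What the plan says.** All of this is in Section IV of the protocol, under Project Design.

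- **Amodiaquine (AQ) basis**, under Intermittent preventive treatment: "AQ will administered on the base of 10 mg/kg daily for 3 days".
- **SP basis**, same paragraph: "SP will administered as a single dose of 25mg/kg of sulphadoxine + 1.25 mg of pyrimethamine". Sulfadoxine is given per kilogram. Pyrimethamine is given in mg with no per-kilogram unit.
- **Table 2** has three weight bands. The columns are the daily AQ dose, then the sulfadoxine and pyrimethamine content of the single SP dose: "5-9 kg 70 mg 175 mg 8.75 mg", "10-18 kg 140 mg 350 mg 17.5 mg" and "19 kg+ 220 mg 550 mg 26.25 mg".
- **Manufacture**: the same paragraph says whole tablets will be made at the exact daily AQ dose and the full SP dose, so that none need be split.
- **Eligibility**, under Recruitment and randomization: the only inclusion criterion bearing on size is "Age 3 – 59 months". Weight is measured at screening, but no criterion uses it. Severe malnutrition is an example of an excluding chronic illness, with no weight cut-off attached.

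**The concern.** Table 2 is in effect the specification for purpose-made product. The Budget Narrative says a manufacturer for the active drugs and matching placebo had been hard to find. If one entry in the table is a slip, it becomes the tablet given to active-arm children in the top band, at up to three rounds. Once tablets exist, correcting the text no longer corrects the product.

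The gap below 5 kg is a different kind of problem. The dosing scheme is narrower than the population that the eligibility criteria admit. The plan does not say what happens to a randomised child who falls outside every band, so sites could handle such a child differently.

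**Working it through.** **Inputs.** The basis is AQ 10 mg/kg per day, sulfadoxine 25 mg/kg, and pyrimethamine 1.25 mg, read here as 1.25 mg/kg. The tablet strengths are the three rows of Table 2.

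**Formulas.** Weight implied by a component = tablet strength in mg ÷ stated mg per kg. Stated SP ratio = 25 ÷ 1.25 = 20:1.

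**Step 1: do the lower rows reproduce?**

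| Band | AQ ÷ 10 | Sulfadoxine ÷ 25 | Pyrimethamine ÷ 1.25 | Ratio |
|---|---|---|---|---|
| 5-9 kg | 70 ÷ 10 = 7 kg | 175 ÷ 25 = 7 kg | 8.75 ÷ 1.25 = 7 kg | 175 ÷ 8.75 = 20.0 |
| 10-18 kg | 140 ÷ 10 = 14 kg | 350 ÷ 25 = 14 kg | 17.5 ÷ 1.25 = 14 kg | 350 ÷ 17.5 = 20.0 |

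Both rows reproduce exactly. This also supports reading the pyrimethamine figure as per kilogram. Taken literally as 1.25 mg in total, it would disagree with every row (8.75, 17.5 and 26.25 mg are 7, 14 and 21 times larger).

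**Step 2: the top row.**

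| Band | AQ ÷ 10 | Sulfadoxine ÷ 25 | Pyrimethamine ÷ 1.25 | Ratio |
|---|---|---|---|---|
| 19 kg+ | 220 ÷ 10 = 22 kg | 550 ÷ 25 = 22 kg | 26.25 ÷ 1.25 = 21 kg | 550 ÷ 26.25 = 20.95 |

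No single weight gives both printed SP figures on the stated basis.

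**Step 3: size, shown from both sides.** At 20:1, 550 mg sulfadoxine pairs with 550 ÷ 20 = 27.5 mg pyrimethamine, and 26.25 mg pyrimethamine pairs with 26.25 × 20 = 525 mg sulfadoxine. The printed pyrimethamine is 26.25 ÷ 27.5 = 0.955 of the figure that matches the printed sulfadoxine, a gap of about 4.5%. Both pairings are arithmetic consequences of the stated ratio. Neither is offered as the correct dose.

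**Step 4: coverage of the eligible population.** The age criterion starts at 3 months and carries no weight condition. Table 2 starts at 5 kg, and no passage gives a rule for a lighter child. The documents contain no weight distribution, so the number of such children cannot be calculated.

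**The case against.** - **The reference weights are back-calculated.** The plan states no 7, 14 or 22 kg. The top band is open-ended, and each printed figure taken alone meets its stated mg/kg at a weight inside the band (22 kg for sulfadoxine, 21 kg for pyrimethamine). This stands: the anomaly is only in the pairing. But the pairing breaks a ratio that the basis and both other rows keep exactly.
- **The mismatch is small beside the spread that banding accepts.** In the two lower bands pyrimethamine runs from 8.75 ÷ 5 = 17.5 ÷ 10 = 1.75 mg/kg to 8.75 ÷ 9 = 17.5 ÷ 18 = 0.97 mg/kg, about +40% to −22% around 1.25. This stands, and it limits the severity. Variation within a band is by design, however; a changed ratio between two components of one dose is not.
- **The missing unit misleads nobody who reads the table.** Largely true, since the lower rows fix the meaning. It matters because the sentence as printed cannot be used to settle the top row.
- **Few children may weigh under 5 kg.** The superseded age-based table gives an average of 6 kg at 4-6 months, and the malnutrition exclusion may remove some lighter children. That makes the case less common but does not close it, since an average does not exclude lighter children, least of all at 3 months.

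Three stronger readings are tempting, and the documents do not support them. First, a reader might infer that the protocol carries two competing top-band doses, because the amendment summary prints "550 mg + 26.75 mg for 19+kg". That figure appears only in the summary of changes. The current Table 2 and the amendment's replacement table both print 26.25 mg, so the operative text has one value. Second, since AQ and sulfadoxine agree at 22 kg, a reader might infer that pyrimethamine is the wrong entry. The agreement is suggestive but settles nothing: the ratio is restored equally well from either side. Third, a reader might infer that every child in the band is affected. Those allocated to placebo are not.

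**Conclusion.** The point holds as a consistency error in one row, together with a coverage gap. The 19 kg+ row pairs SP components that correspond to 22 kg and 21 kg, at 20.95:1 instead of 20:1, a mismatch of about 4.5%. This rests on reading the pyrimethamine basis as 1.25 mg per kg, which both lower rows bear out. The effect is confined to active-arm children in the top band, whose number the documents do not give, and no clinical consequence is claimed.

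The gap below 5 kg is real on the face of the eligibility criteria and Table 2. Its size is unknown and may be zero. How such a child would in practice be handled is not stated, so ad hoc dosing or omission is a possibility and not a finding.

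Nothing here touches the primary endpoint, sample size, power or comparison of arms. It warrants a correction before manufacture, and does not amount to a fault in the design.

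**What to change.** Before tablets are manufactured and children enrolled:

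1. Reconcile the 19 kg+ row of Table 2 with the sentence giving the mg/kg basis, and complete that sentence's pyrimethamine unit. The clinical team decides which figures stand. If the difference in ratio is intended, say so beneath the table.
2. Check the manufacturing order against the reconciled table.
3. Reconcile the eligibility criteria with the lowest weight band, so that every child who can be randomised is covered by the dosing text. How this is done is a clinical decision.

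The cost is a few lines of text and one check of the order while tablets have not yet been made. It would be higher once they had been.
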